## Abstract

**Background:**

Shifts in the gastrointestinal microbiome have been shown to contribute to the progression of metabolic diseases including prediabetes and type 2 diabetes mellitus. Research suggests that *in-vivo* modulation of the gut microbiome by specific probiotic microorganisms may improve insulin sensitivity and blood sugar management, preventing or delaying the development of type 2 diabetes mellitus. However, further research is needed to understand the effect of probiotics as a therapy for the treatment of metabolic diseases. An evidence-based multi-species probiotic was developed to encourage a shift in the gastrointestinal bacterial cohort from a disease-prone to a balanced state with the aim of improving metabolic markers associated with type 2 diabetes mellitus.

**Methods:**

Sixty adults with a body mass index ≥25 kg/m^2^ with prediabetes or type 2 diabetes mellitus (diagnosed within the previous 12 months) will be enrolled in a double-blind, placebo-controlled pilot study. Participants will be randomized to a multi-species probiotic or placebo for 12 weeks. Both groups will receive lifestyle and nutritional advice. The primary outcome measure is the change between groups in fasting plasma glucose levels from baseline to 12 weeks. Secondary outcome measures include, but are not limited to, the change in lipid profile, systemic inflammation, gut permeability, and faecal microbial and metabolomic profiles. Blood and stool samples are collected at baseline and 12 weeks after treatment.

**Discussion:**

Intentional manipulation of gastrointestinal microbial profiles may be useful for preventing and controlling type 2 diabetes mellitus and its associated metabolic complications.

**Trial registration:**

Australian New Zealand Clinical Trials Registry, ACTRN12613001378718. Registered on 16 December 2013.

**Electronic supplementary material:**

The online version of this article (doi:10.1186/s13063-016-1762-x) contains supplementary material, which is available to authorized users.

## Background

The relationship between the gastrointestinal microbiota and obesity-associated disorders has gained extensive research interest in the past 10 years. A disturbed gut microbiota expressed as gut dysbiosis (an intestinal physical barrier abnormality) has been associated with the progression and maintenance of obesity, type 2 diabetes mellitus, cardiovascular diseases and metabolic syndrome [1–5]. The mechanisms by which gut dysbiosis produces and influences these metabolic alterations are via regulation of the host’s energy balance and storage and by promoting endotoxaemia or bacteraemia [6]. Furthermore, postprandial blood glucose levels are very much influenced by the gut bacteria, with recent research demonstrating a profound influence on how individuals responded to identical food items that could be accurately predicted based on their gut bacterial profiles [7]. Gut dysbiosis may be restored to a balanced state through microbiota-based interventions, which may improve metabolic markers associated with type 2 diabetes mellitus through immunomodulatory and anti-inflammatory pathways.

A probiotic is a microbiota-based intervention defined as ‘a live microorganism, which, when administered in adequate amounts, confers beneficial health effects on the host’ [2, 8, 9]. A meta-analysis evaluating the effect of probiotics on glycaemia suggests that probiotics can play an important role in the prevention and treatment of type 2 diabetes mellitus [10]. Certain probiotic species have improved insulin sensitivity, inflammatory markers and lipid profiles in obese, type 2 diabetes mellitus and dyslipidaemic subjects [11–13]. However, it is not known whether a combination of probiotic species that have demonstrated beneficial therapeutic effects individually can improve metabolic markers associated with type 2 diabetes mellitus and have an additive effect to standard care. Therefore, we have formulated a novel prescription containing eight probiotic species that belong to the *Lactobacillus*, *Bifidobacterium*, *Streptococcus* and *Saccharomyces* genera to improve glucose metabolism in subjects with prediabetes and early type 2 diabetes mellitus*.* This multi-species probiotic formula has been tested previously in our laboratory using *in-vitro* models with rodent fat and muscle cell lines. The results from these *in-vitro* experiments showed the supernatants collected from the growth media of the probiotic decreased lipid accumulation in 3T3-L1 adipocytes and restored glucose uptake in insulin resistant L6 muscle cells [7]. The formulation and dosage proposed in this study have not been investigated previously in human studies. Therefore, the aim is to test the safety and efficacy of this novel probiotic formulation in adults with prediabetes and early type 2 diabetes mellitus. We hypothesize that a shift in the gut microbiome induced by this multi-species probiotic will decrease metabolic and inflammatory markers and result in improved blood glucose management.

## Methods

### Design

This pilot study is a single site, randomized, double-blind, placebo-controlled clinical trial conducted at the Charles Perkins Centre Royal Prince Alfred Clinic in Sydney, Australia. Sixty adults with prediabetes or early type 2 diabetes mellitus will be randomized to take either a multi-species probiotic capsule or placebo for 12 weeks. The Standard Protocol Items: Recommendations for Interventional Trials (SPIRIT) was used to elaborate the study protocol (see Additional file 1). Participants’ progression through the trial is presented in Fig. 1 (CONSORT diagram [14]).

**Fig. 1 Fig1:**
[figure not shown]
CONSORT flowchart of participants’ progress through the study

### Recruitment process

Subject recruitment will be through the Boden Institute’s clinical trials register, the Sydney Local Health District intranet, the University of Sydney website and Diabetes Australia social media channels.

### Allocation

Participants will be randomized to the probiotic or placebo group without stratification using computer-generated random numbers (FileMarker Pro). Both participants and study investigators will be blinded to treatment allocation. Participant unblinding will only be requested in a medical emergency, where knowledge of the study treatment is essential for any treatment of the participant. The reason for unblinding will be documented and the study treatment will not be revealed to any member of the study team.

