### Data analysis and statistical considerations

#### Sample size

As this is a pilot study, no evidence about blood glucose differences is available for this product. Therefore, it was decided to use the number of participants needed to detect a mean difference between the groups in fasting plasma glucose level of 2.0 mmol/l (standard deviation 2.0 mmol/l) at week 12 with 80% power and 95% confidence as a starting point. The number of subjects needed is 32. The fact that the study includes two different cohorts (participants with prediabetes and early type 2 diabetes mellitus) was also taken into consideration, as owing to the lack of stratification at randomization the variance could be high. Therefore, the sample size has been inflated to 30 per group (including a drop-out rate of 25%) to give a total sample size of 60 eligible participants.

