#### Statistical analysis

Analysis will be conducted using the intention-to-treat principle and missing data will be imputed with baseline values for a conservative estimate (i.e. no change). Descriptive statistics will be presented as mean ± standard deviation, or median with range, as appropriate. Primary and secondary outcomes will be analyzed using generalized linear models. The following covariates will be added to the model: sex, age and percentage weight change. Additionally, if there is an imbalance between the groups of prediabetes and type 2 diabetes mellitus, this will be included as a covariate in the model. Three planned subgroup analyses will be completed between participants who are taking metformin, participants classified as prediabetic or type 2 diabetes mellitus and participants defined as compliant. Chi–square analysis will determine associations between categorical variables.

For the gut microbiome analysis, sequenced data will be interpreted using the bioinformatics tools programmed in the Ion Reporter™ software. Quantitative Insights Into Microbial Ecology (QIIME) algorithms will determine the bacterial diversity within a sample (alpha diversity) and between all the samples (beta diversity). Additionally, multivariate data analysis with principal component analysis on the diversity indexes and comparisons of genus and species level data will be performed to reveal differences in the microbial composition between the two groups. Differences in relative abundance of taxa between the intervention and placebo group and between participants receiving and not receiving metformin will be determined using ANOVA, using subject as a blocking factor. Changes in relative abundance will be tested for correlations with patient biochemical measurements. For all statistical tests, the Benjamini–Hochberg false discovery rate adjustment [20] will be used to account for the number of taxa tested in each comparison.

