## Discussion

This randomized trial will assess the efficacy and safety of a multi-species probiotic formulation in the management of prediabetes and type 2 diabetes mellitus metabolic markers. The study outcomes may lead to novel treatments to reduce the metabolic disturbances associated with these disorders. This study will also provide empirical evidence to address currently unresolved issues with the efficacy and safety of probiotics. In designing this clinical study, several key decisions were made to overcome current limitations in the published literature and reduce possible biases.

While focusing on those with prediabetes, subjects with early type 2 diabetes mellitus were included to assess the feasibility of inducing partial or complete remission of type 2 diabetes mellitus. This decision also meant including participants taking metformin as this drug is commonly prescribed early in type 2 diabetes mellitus; it has also been shown to have effects on the microbiome [21, 22]. Furthermore, microbiota-based interventions may reduce gastrointestinal symptoms associated with metformin administration with a consequent improvement in medication compliance [23]. As far as we are aware, the interaction between the gastrointestinal microbiota, probiotics and metformin has not been explored in patients with prediabetes and type 2 diabetes mellitus. Therefore, this study will assess the efficacy and safety of a novel multi-species probiotic and provide preliminary data on its effect on metformin.

Limitations of the study include the short-term impact of the intervention, as subjects will be treated for only 12 weeks. Additionally, the small number of visits during the study can be considered a risk factor for non-compliance. Moreover, it must be remembered this study is investigating the short-term impact of a multi-species probiotic formulation to help improve fasting blood glucose levels. It is known that probiotics do not recolonize the intestinal tract but rather are transient colonizers and that wash-out of administered doses can take from approximately 4–6 weeks, thereby leading to a therapy that may be not be permanent.

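### Diabetes status is named as a source of high variance, yet it is neither stratified on nor always adjusted for; the sample size is raised instead

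*Protocol article*

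**What the plan says.** - **Allocation:** "Participants will be randomized to the probiotic or placebo group without stratification using computer-generated random numbers".
- **Sample size:** the calculation starts from a gap between the two arms in "fasting plasma glucose level of 2.0 mmol/l (standard deviation 2.0 mmol/l) at week 12". Power is set at 80% and confidence at 95%, and the result is: "The number of subjects needed is 32". Two cohorts are enrolled, and "owing to the lack of stratification at randomization the variance could be high". Hence "the sample size has been inflated to 30 per group (including a drop-out rate of 25%) to give a total sample size of 60". The increase is not divided between drop-out and variance.
- **Statistical analysis:** primary and secondary outcomes go into generalized linear models with sex, age and percentage weight change. Diabetes status joins them only if the groups turn out unequal on it. What counts as unequal is not defined. The section continues: "Three planned subgroup analyses will be completed between participants who are taking metformin, participants classified as prediabetic or type 2 diabetes mellitus", plus a compliance subgroup.
- **Discussion:** of metformin, "it has also been shown to have effects on the microbiome".
- **Inclusion criteria and Clinical examination:** diabetes status is settled by eligibility and medication is recorded at screening, so both factors are known before randomisation.

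**The concern.** The protocol identifies a prognostic baseline factor, says that ignoring it costs variance, and then uses neither of the two standard tools in full. It does not stratify, and it adjusts only conditionally.

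The conditional rule is the weaker part. A covariate is worth fitting because it explains outcome variation, whether or not the arms differ on it. When the arms are balanced, leaving it out keeps the between-cohort variation in the residual, and the test becomes conservative. With no threshold, the decision whether to adjust the primary analysis is also made after the allocation is seen.

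Two things are at stake: precision for fasting plasma glucose in a trial of 60, and usable arm sizes inside the diabetes-status and metformin subgroups. More participants answer the first only by brute force and do not balance the arms within those subgroups.

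**Working it through.** **1. The protocol's own figure.** Difference 2.0, SD 2.0, 80% power, 95% confidence read as two-sided 5%:

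n per arm = 2 × (1.960 + 0.842)² × 2.0² / 2.0² = 15.7, so 16 per arm and 32 in total. The stated figure reproduces. A t-test calculation gives 17 per arm, 34 in total.

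**2. Drop-out.** 16 / 0.75 = 21.3, so 22 per arm and 44 in total. 60 − 44 = 16 participants remain. Applied to the total, 32 / 0.75 = 42.7, so 43 and a remainder of 17. From the t-test figure, 17 / 0.75 = 22.7, so 23 per arm, 46 in total and a remainder of 14.

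**3. What the allowance buys.** 60 × 0.75 = 45 completers, 22.5 per arm. The largest SD that keeps 80% power for 2.0 mmol/l is 2.0 × √(22.5/2) / 2.802 = 2.39 by the normal approximation, and about 2.34 by t-test.

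**4. What cohort difference that covers.** If 2.0 is the SD within a cohort, p the share in one cohort and D the difference between cohort means, the SD within an arm is √(2.0² + p(1 − p)D²). Setting it to 2.39 gives D of about 2.6 mmol/l at a 50:50 mix, 2.9 at 30:70 and 3.3 at 20:80. The protocol gives neither mix nor D.

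**5. Which tool recovers the loss.** Simulation with D = 2.6, a 50:50 mix, within-cohort SD 2.0, blocks of 4 and a true difference of 2.0. Repeat runs moved single cells by about a point.

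| Evaluable | Neither | Stratified list only | Adjustment only | Both |
|---|---|---|---|---|
| 32 | 63% | 65% | 77% | 78% |
| 45 | 78% | 82% | 90% | 90% |

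At 32 evaluable, the stratified list lowers the true standard error of the treatment difference from about 0.85 to 0.71. The unadjusted test does not use this: its type I error falls to about 2% instead of power rising. Adjustment without stratification reaches nearly the same standard error and does use it.

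**6. Sensitivity to D.** With D = 1.0 at a 50:50 mix, the variance ratio is (4 + 0.25 × 1.0²) / 4 = 1.06, against (4 + 0.25 × 2.6²) / 4 = 1.42 for D = 2.6. Little is then left to recover.

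**7. Balance in the subgroups.** With a 50:50 mix and equal arms, the share with type 2 diabetes differs by 20 points or more between arms in about 15% of trials at 60 and 18% at 45. With an assumed 15 metformin users and arms held at 30:30, one arm gets 5 or fewer in 23% of trials; with 20 users, one arm gets 6 or fewer in 5%. A 5:10 split widens that subgroup's standard error by √((1/5 + 1/10) / (2/7.5)) = 1.06, and a 6:14 split by √((1/6 + 1/14) / (2/10)) = 1.09.

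**The case against.** The protocol discloses its choice and does not rely on numbers alone: diabetes status enters the models if the arms differ on it. Chance imbalance in the primary and secondary outcomes is therefore partly handled. This stands, and it means that the plan's power lies somewhere between the unadjusted and adjusted columns, depending on a threshold that is not given.

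The allowance of 16 is an inference, and the protocol calls 32 only a starting point for a pilot. The primary outcome is change from baseline, so part of the difference in glucose level between cohorts may cancel. Both points stand and limit the size of the claim. The subgroup penalties of 6% and 9% are also modest, and subgroups of this size will be imprecise in any case.

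Three stronger readings are tempting but not supported:

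- **That a stratified list would largely remove the variance problem and so save the 16.** Mixing cohorts raises the variance within each arm whichever list is used. The gain comes from the model term.
- **That blocking is absent because it is not mentioned.** An article commonly leaves such detail to the full protocol.
- **That the taxa analysis ignores metformin.** The Statistical analysis section compares users with non-users and blocks on subject. With stool taken at baseline and week 12, stable differences between participants may well cancel.

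**Conclusion.** The concern holds in a limited form. The protocol names the cohort mix as a source of variance but makes adjustment for it conditional on an undefined imbalance, and it leaves allocation unstratified on two factors that are known at screening and used for planned subgroups.

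The main loss is from not always fitting diabetes status: up to about 12 to 14 points of power for the primary outcome (63% to 76–77% at 32 evaluable, 78% to 90% at 45). This is an upper figure. It compares never with always adjusting, and it rests on a 2.6 mmol/l difference between cohorts that was solved from the protocol's own allowance, not taken from data. If the cohorts differ by about 1 mmol/l in the analysed outcome, the gain nearly disappears. The unstratified list costs little primary power (about 1 to 4 points); what it costs is balance inside small subgroups.

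**What to change.** 1. **Statistical analysis:** replace the conditional rule. Always include diabetes status (prediabetes or type 2 diabetes) as a covariate in the primary and secondary outcome models.
2. **Allocation:** for participants still to be randomised (the Trial status section says recruitment is ongoing), stratify the list by diabetes status, and by metformin use if stratum sizes allow. Apply the metformin stratum across both cohorts, since the inclusion criteria allow metformin in either. The main purpose is balance inside the planned subgroups.
3. **Sample size:** attribute the allowance to differences between the cohorts, not to the lack of stratification, and state the SD that 45 completers tolerate: about 2.34 mmol/l by t-test for a 2.0 mmol/l difference at 80% power.

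Cost: a short amendment, a new list and one more model term. Small strata may end with incomplete blocks, and stratification helps only participants not yet randomised, whose number the article does not give. The first and third changes do not depend on that number; the first should be made before unblinding.

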### Data handling and record keeping

Data is completed on case report forms, source documents (both written on paper and time and date stamped electronic capture) and entered into a database. This database will be password protected and backed up the University of Sydney server. All results will be sent to participants by email.

### Inclusion criteria

Participants are eligible for the study if they meet the following criteria:Aged ≥ 18 yearsBody mass index ≥ 25 kg/m^2^
Have prediabetes or have been diagnosed with type 2 diabetes mellitus within the previous 12 monthsAre treated by diet alone or diet plus metforminAre willing to adhere to the study protocol (no yoghurt, fermented food, dietary supplements, probiotics or prebiotics) for the duration of the study.

The definition of prediabetes is based on the American Diabetes Association guidelines [15] and participants must have: (i) a fasting plasma glucose level between 5.6 mmol/l and 6.9 mmol/l or; (ii) two-hour post-challenge (oral glucose tolerance test) plasma glucose level between 7.8 mmol/l and 11 mmol/l or; (iii) HbA1c between 5.7% and 6.4%.

The criteria for the diagnosis of type 2 diabetes mellitus is based on the American Diabetes Association guidelines [15]. Participants are included in the study if they have been diagnosed with type 2 diabetes mellitus by their general practitioner in the previous 12 months or have: (i) a fasting plasma glucose level ≥ 7.0 mmol/l or; (ii) 2-hour post-challenge (oral glucose tolerance test) plasma glucose level ≥ 11.1 mmol/l or; (iii) an HbA1c ≥ 6.5%.

### Exclusion criteria

Type 1 diabetes mellitusType 2 diabetes mellitus diagnosed for longer than 12 monthsTaking anti-obesity drugs or blood glucose-lowering medications (i.e. sulfonylureas, alpha-glucosidase inhibitors, thiazolidinediones and glucagon-like peptide-1 analogues) other than metforminConcomitant gastrointestinal disorders (i.e., irritable bowel syndrome, inflammatory bowel disease and coeliac disease)Recent use (within the previous 4 weeks) of antibiotics and dietary supplements (fish oil, probiotics, prebiotics, multivitamins, minerals, nutraceuticals and herbal preparations)Pregnancy, breastfeeding or planning to become becoming pregnantAlcohol abuse or the use of any illicit drugsClinical evidence of active infection or any severe illness unrelated to diabetes.

### Intervention and compliance

#### Investigational product

The study coordinator will obtain written informed consent and randomize eligible participants to the multi-species probiotic or placebo. The study product contains either 50 × 10^9^ colony forming units (cfu) of a multi-species probiotic (27 × 10^9^ cfu of *Lactobacillus* spp., 22.5 × 10^9^ cfu of *Bifidobacterium* spp., 450 × 10^6^ cfu of *Streptococcus* spp. and 45 × 10^6^ cfu of *Saccharomyces* spp., patent pending) or 50 mg of the placebo (maltodextrin) per capsule. The probiotic and placebo capsules are opaque white and look and smell identical. Verbal and written instructions on how to take the study product or placebo will be provided at the initial and each review visit. Enrolled participants will be required to:Take two capsules twice per day (20 min before breakfast and dinner) with cold non-carbonated water. The product is not to be mixed or taken with hot drinks or foods, as heat and stomach acids can reduce the stability of the probiotic bacteriaStore the study product in the fridge at 4–6 °CRecord the number of capsules taken each day in the study diaryBring all capsules remaining in the bottle to the next visitAvoid eating or drinking yoghurt, fermented food, dietary supplements (i.e. vitamins, minerals, nutraceuticals, herbal preparations, probiotics, prebiotics or fish oils) and antibiotics (unless recommended by a health professional).

#### Study product compliance

Capsule counting, at weeks 6 and 12, will be used to assess the participant’s compliance in taking the study product. A record of the date, the visit and the amount of study product dispensed and returned will be documented for each participant. Participants are defined as non-compliant if they have taken less than 80% of the study product on both occasions.

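### The compliance rule fails a participant only if both capsule counts are under 80%, so very uneven intake totalling as little as 40% can enter the compliant-participant analysis

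*Protocol article*

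**What the plan says.** Under Study product compliance, the article sets two counting occasions: "Capsule counting, at weeks 6 and 12, will be used to assess the participant’s compliance in taking the study product". It then gives its only definition: "Participants are defined as non-compliant if they have taken less than 80% of the study product on both occasions". It does not define compliant separately, and it gives no threshold for total intake over the trial.

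The schedule comes from two other places. Under Investigational product, participants are told: "Take two capsules twice per day (20 min before breakfast and dinner". Under Design, they "will be randomized to take either a multi-species probiotic capsule or placebo for 12 weeks".

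The definition is used under Statistical analysis. Three subgroup analyses are planned there: one by metformin use, and the others concerning "participants classified as prediabetic or type 2 diabetes mellitus and participants defined as compliant". The same section says that the analysis follows the intention-to-treat principle.

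**The concern.** An analysis limited to compliant participants is normally meant to show the effect in people who had adequate exposure. The rule as written does not secure that. Because a participant must fall below 80% at both counts to be called non-compliant, a single adequate period is enough to stay in the set, whatever happened in the other one.

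The participant who takes the product for six weeks and then stops matters most. The primary outcome is the change in fasting plasma glucose to week 12. The Discussion says that administered probiotics do not colonise the gut permanently and wash out over roughly 4 to 6 weeks. Someone who stopped at week 6 would therefore be at the upper end of that interval when the endpoint is measured, yet could be analysed as compliant. A null result in this set would then be hard to interpret.

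A second matter concerns the label. Metformin use and diabetes status can be fixed at baseline. Compliance is observed only after randomisation, so comparing the arms among compliers is not protected by the randomisation in the way a baseline subgroup comparison is.

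**Working it through.** The article gives no compliance total, so there is no stated figure to reproduce. The check asks what the rule admits.

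**Inputs**
- Capsules per day: 2 × 2 = 4 (Investigational product).
- Duration: 12 weeks = 84 days (Design), with counts at weeks 6 and 12 (Study product compliance), so two periods of 42 days.
- Threshold: 80% at each count; non-compliant only if below it at both (Study product compliance).

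**Scheduled capsules**
- Per period: 4 × 42 = 168.
- Whole trial: 4 × 84 = 336.
- 80% of one period: 0.8 × 168 = 134.4, so 135 whole capsules reach the threshold and 134 do not.

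**Rule as written**
- 135 in one period and 0 in the other: below 80% on one occasion only, so not non-compliant. Overall intake is 135/336 = 40.2%. Checking every whole-capsule pair from 0 to 168 per period confirms this as the minimum.
- 132 in each period: 132/168 = 78.6% both times, so non-compliant, with 264/336 = 78.6% overall.
- The highest intake that is still non-compliant is 134 + 134 = 268/336 = 79.8%.

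**Sensitivity to the reading**
- If the week 12 count is read as cumulative from baseline, 135 then 0 still passes at week 6, and the minimum stays at 40.2%.
- Apart from whole-capsule rounding, the result does not depend on the number of capsules per day: half the schedule at 80% is 0.5 × 80% = 40%.
- If visits fell unevenly (an assumption: 5 and 7 weeks), the shorter period has 4 × 35 = 140 capsules, 80% of which is 112, and the minimum is 112/336 = 33.3%.

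**Alternative rules**
- Non-compliant if below 80% on either occasion: minimum 135 + 135 = 270/336 = 80.4%.
- Compliant if at least 80% of the total: 0.8 × 336 = 268.8, so minimum 269/336 = 80.1%.

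**Time off product that each alternative still allows before week 12**
- Total-intake rule: 269/4 = 67.25 days of full intake, leaving 84 − 67.25 = 16.75, about 17 days.
- Each-period rule: 135/4 = 33.75 days of full intake in the second period, leaving 42 − 33.75 = 8.25, about 8 days.

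**The case against.** The strongest reply is that 40% is a corner of the rule, not its usual behaviour. It needs just over 80% in one six-week period and nothing in the other. That stands. A participant who takes 40% evenly is below 80% at both counts and is correctly called non-compliant. A reader might infer that anyone on 40% passes, or that the rule ranks participants backwards in general. Neither follows: the misordering arises when uneven intake is compared with even intake.

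It can also be said that the wording may be loose for the two counts taken together, and that compliant is only inferred to be the complement of non-compliant. Either is possible, but the literal reading is the natural one and no other definition is offered. If something else was meant, the sentence still needs correcting.

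A reader might infer a definite dilution of the treatment effect. If a share p of the compliant set had stopped and kept no effect at week 12, the estimate would shrink by the factor 1 − p. The article gives no basis for p. The 25% drop-out allowance in the sample size is not a rate of stopping midway while still attending. Nor does the article say how a missing week 12 count is classed, so the argument is secure only for people who stop but return for counting.

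Finally, the consequence is limited. The rule feeds one secondary analysis in a 60-person pilot. How unreturned bottles are handled and whether subgroups are tested by interaction are details commonly left to an analysis plan, so they are not part of this point.

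**Conclusion.** The point holds in a limited form. Under the literal rule, with compliant meaning not non-compliant and two equal six-week periods, a participant with very uneven intake can be classed as compliant on as little as 135/336 capsules (40.2%). One such participant is the person who takes nothing in the six weeks before the primary endpoint. Meanwhile 264/336 (78.6%), evenly spread, is non-compliant.

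A reader might go further and infer bias in the main result. The documents do not support that: the primary analysis follows intention to treat and does not use this definition. What is affected is the compliant-participant analysis, by an amount that cannot be derived from the article. Calling that analysis a subgroup is a separate, smaller fault, since its membership is determined after randomisation. The article makes no causal claim for it, but the label puts it on the same footing as the baseline subgroups.

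**What to change.** Replace the definition used for the analysis set with one of these:
- compliant means at least 80% of scheduled capsules in each of the two counting periods, that is, non-compliant if below 80% on either occasion; or
- compliant means at least 80% of the 336 capsules scheduled over the 12 weeks.

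Both guarantee just over 80% overall. The first also limits how long a participant can have been off product before week 12 (about 8 days at full intake until stopping, against about 17 under the second), so it fits the purpose of the analysis better. Neither secures intake right up to the endpoint, and the text should not imply that it does.

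Report the compliant-only comparison as a supportive per-protocol analysis, apart from the subgroups by metformin use and diabetes status.

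The cost is small: a sentence on the definition and a change of label, using dispensed and returned amounts that are already recorded. Somewhat fewer participants will be classed as compliant, so that analysis will be less precise. Recruitment was still under way when the article was written; the change should be made before unblinding.
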